## **Tertiary Outcome Measures**

### ***Neonatal***

- 1) Delivery Room**
  - Apgar scores (1, 5, 10 minutes)
  - Umbilical cord venous and arterial pH
  - Intubation in delivery room
  - Chest compressions or epinephrine
  - Volume bolus given in delivery room
- 2) First 24 hours after birth**
  - NICU Admission temperature
  - Red blood cell transfusion
  - Highest hematocrit (before transfusion)
  - Lowest mean arterial blood pressure
  - Any volume bolus in the first 24 hours including in the delivery room, and including NICU packed red blood cells, platelets, plasma, saline, other fluid bolus
  - SNAPPE-II score (Score for Neonatal Acute Physiology-Perinatal Extension) in the first 12 hours after birth
- 3) First 10 days after birth**
  - Surfactant administration
  - Days on mechanical ventilation
  - Highest bilirubin
  - Days on phototherapy
- 4) Hospital course until 36 weeks' PMA**

**PI: [name] Version**

**Date: August 29, 2023**

- IVH (most severe grade during hospitalization)
- Cerebellar hemorrhage
- Cystic periventricular leukomalacia (cPVL)
- Patent Ductus Arteriosus (PDA) requiring pharmacological or surgical treatment
- Early-onset septicemia (<72h from birth) (positive blood culture and at least 5 days of antibiotic therapy)
- Spontaneous intestinal perforation (SIP) requiring surgery or peritoneal drain
- Necrotizing enterocolitis (Modified Bell's stage 2-3)
- Bronchopulmonary dysplasia (receiving continuous supplemental oxygen at 36 weeks PMA)
- Severe ROP (stage 3 or treated with laser or bevacizumab) prior to 36 weeks PMA

## **Safety**

Safety will be monitored in all randomized/on-study mothers and infants by comparing primary and secondary outcomes and reportable adverse and serious adverse events between study arms, as described in sections 8 and 9. This includes but is not limited to outcomes reported to be different in preterm infants undergoing delayed versus immediate cord clamping such as hematocrit in the first 24h after birth, bilirubin in the first 10d after birth, indicators of adverse cardiovascular transition in the delivery room and first 24h after birth, intraventricular hemorrhage, and other complications of extreme prematurity. The UVA Study Team and DSMC will regularly review these events and diagnoses for differences between study arms and differences from standard rates for EPT infants in international databases such as Vermont Oxford Network.

## 7 STATISTICAL CONSIDERATIONS

### Study Design

The study is designed as a Phase III, randomized, multicenter comparative study of standard 30-60 seconds cord clamping with ventilatory assistance after cord clamping (Standard) versus 120 seconds cord clamping with ventilator assistance prior to cord clamping (VentFirst) in extremely preterm infants (EPT, 230/7 – 286/7 weeks' gestational age(GA)). Specifically, the study is designed to estimate the difference in survival without IVH on the first head ultrasound 7-10 days following birth between the two interventions in two cohorts of EPT infants.

|                                   |                                                                                                                                                                                                   |         |
|-----------------------------------|---------------------------------------------------------------------------------------------------------------------------------------------------------------------------------------------------|---------|
| two cohorts:               | 1) EPT infants not breathing well 20-30 seconds from delivery (apneic or gasping)
2) EPT infants breathing well 20-30 seconds from delivery (crying or breathing regularly)      |         |
| two stratification factors | 1) Gestational age ( 2 levels):
GA 23 0/7 – 25 6/7 weeks; GA 26 0/7 – 28 6/7 weeks                                                                 | 2) Site |
| two interventions:         | Arm 1) "Standard" (30-60 seconds cord clamping) with ventilatory assistance after cord clamping
Arm 2) "VentFirst" (120 seconds cord clamping with ventilatory assistance from 30-120 seconds) |         |

### Accrual

We recognize that target accrual will be limited by two major factors:

- 1) Ability to obtain informed consent (some mothers will deliver before consent can be obtained, and others will decline the study)
- 2) Of the mothers giving informed consent, some will deliver before 23 or after 29 weeks and others will deliver very quickly before randomization and equipment set-up can be accomplished.

Taking into account these restrictions, we anticipate being able to enroll, randomize, and carry out the study protocol on ~ 35 to 40% of the estimated 2500 EPT deliveries over the study period. Target accrual is estimated at 940 eligible EPT infants, thus, accrual to the study should be completed within 4 ½ years of study initiation with yearly accrual rates of approximately 10%, 20%, 25%, 25% and 20% of the total.

### Randomization and stratification

For this study, the randomization unit is the mother and the analysis unit is the EPT infant. Thus, twins are assigned the same intervention. Within

each site, mothers will be stratified by expectant infant GA categories without regard to cohort. Initial randomization will occur with equal allocation to each arm using a stratified block randomization scheme with varying block sizes (of size 2-6). Although we cannot determine cohort designation (breathing well or not) at randomization, given the large target sample size we assume that the randomization process will result in approximate balance between arms within cohort. However, if a significant imbalance is noted in cohort 1 as assessed by the DSMC then a weighted minimization scheme will be used to maintain arm balance within cohort 1. If balance is maintained, infants will continue to be randomized with equal allocation to each arm using the stratified block randomization scheme. Given that a 40/60% or a 30/70% arm imbalance reduces power to 78% or 73%, respectively, the randomization scheme will be modified if a 30/70% arm imbalance is observed in cohort 1, or as deemed appropriate by the DSMC. Note, the probability of a 30/70 split or more extreme in either arm in cohort 1 is  $<0.001$ .

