**Criteria for evaluation:**

**Efficacy:** Head ultrasound imaging 7-10 days after birth and other clinical outcomes

**Safety:** Incidence and severity of Serious Unanticipated Events, SAEs and AEs determined to be related or possibly related to the intervention.

**Statistical methods:** The study is designed as a Phase III, two-arm, randomized, multicenter comparative study of **Standard** versus **VentFirst** cord clamping in extremely preterm infants in two cohorts of infants (those **breathing well** and those **not breathing well**). Analyses will be performed separately within each cohort.

**Efficacy:** The primary analysis will be based on all randomized eligible EPT infants, and will be based on the arm they were randomized to regardless of intervention received (intent-to-treat). The primary outcome of the trial is based upon the central review of the head ultrasound and is the proportion of EPT infants who are alive without any grade IVH on head ultrasound obtained 7-10 days following birth. The primary outcome classification is binary and the stratified Cochran-Mantel-Haenszel test for relative risk will be used for the final comparison of intervention arms.

**Safety:** All randomized EPT infants will be evaluable for adverse events from the time of delivery. Adverse events will be tabulated by frequency and severity, overall and by arm as well as by cohort. Differences in the level of adverse events by study intervention will be assessed by classifying them as severe or not severe and examining the relative proportion of severe events.

LIST OF ABBREVIATIONS

| Abbreviation or specialist term | Explanation                                            |
|----------------------------------------|---------------------------------------------------------------|
| AE                                     | Adverse Event                                                 |
| ACOG                                   | American College of Obstetrics and Gynecology                 |
| AAP                                    | American Academy of Pediatrics                                |
| BPD                                    | Bronchopulmonary Dysplasia                                    |
| CBC/Diff                               | Complete Blood Count and differential                         |
| CPAP                                   | Continuous Positive Airway Pressure                           |

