### **At Delivery**

#### **Initial Steps (both arms)**

- For **vaginal** deliveries, the infant will be placed on a stable surface near the introitus on a warming pad with OB towel and/or plastic drape to prevent hypothermia.
- For **Cesarean section** deliveries, the infant will be placed on the mother's pelvis or a suitable stable surface on a sterilely covered warming pad and sterile OB towel and/or sterile plastic drape.
- A heart rate monitor may be applied.
- The infant will be stimulated to breathe for up to 30 seconds from birth, including bulb suctioning of the mouth and nose if indicated.
- At 20 seconds from birth, the VFF will announce "20 seconds; Neo assess breathing. Is the baby breathing well or not?" The neonatology provider will assess breathing, and at 30 seconds announce "breathing well", or "not breathing well" and the VFF will record this.

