| 26 0/7 to 28 6/7 | 0.62                                     | 74.4%                                           | 25.6%                   |
| combined                               | 1.00                                     | 63.0%                                           | 37.0%                   |

We note that for sample size calculations we do not have numbers by site and thus assume a common effect, resulting in calculations that are based upon a randomized stratified design, which divides the sample among 2 strata at the assumed proportions observed in the VON data, assuming an uncorrected Cochran-Mantel-Haenszel test statistic with a two-sided 5% level test for *each* cohort, separately. Specifically, optimal target accrual for

the primary cohort of interest (cohort 1), summed across all strata, of 172 EPT infants in each intervention arm achieves approximately 80% power to test for a null odds ratio of 1.0 versus an alternative odds ratio of 0.5 (or a difference of 14% in rates). For cohort 2, optimal target accrual of 298 EPT infants in each intervention arm achieves approximately 80% power to test for a null odds ratio of 1.0 versus an alternative odds ratio of 0.55 (or a difference in rates of 12.5%). Shown in the table are estimated power calculations to assess each cohort assuming varying accrual proportions to the two cohorts and alternative odds ratios since accrual to each cohort cannot be controlled. The PASS 11 Power Analysis and Sample Size package was used to generate the sample size estimates.

| For total target accrual of N=940 EPT infants (N=N 1 +N 2 )
Assuming equal allocation (1:1) to intervention arms within each breathing cohort |                                                |                                               |                                        |          |          |
|------------------------------------------------------------------------------------------------------------------------------------------------------------------------|------------------------------------------------|-----------------------------------------------|----------------------------------------|----------|----------|

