If we set total target accrual to 940 eligible EPT infants and assume that at least 37% of accruals fall into cohort 1 then we will have approximately 80% power to detect an odds ratio of 0.5 for VentFirst compared to Standard for cohort 1 and we will have approximately 81% power to detect an odds ratio of 0.59 for VentFirst compared to Standard for cohort 2. Power increases for cohort 1 assessment as the proportion of accruals to that cohort increases and decreases in cohort 2 to as low as 72% for an odds ratio of 0.6. However, increasing our ability to assess the primary hypothesis at the cost of reducing the secondary is reasonable and still provides sufficient power to detect an odds ratio of 0.55. Given these conditions we will require accrual of at least 344 EPT infants to Cohort 1. If our assumptions on accrual proportions are incorrect and more than 65% of EPT infants are being accrued to cohort 2 then accrual to cohort 2 will be halted once 600 EPT infants are accrued.

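### Cohort is declared 30 seconds after birth by unblinded staff, so cohort 2 cannot be halted alone, and re-weighting a cohort 1 imbalance would leave arm-dependent labelling in place

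*Protocol*

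**What the plan says.** Mothers are randomised before delivery, preferably within the last hour (Protocol section 4, Randomization), within site and gestational-age stratum and without regard to cohort (section 7, Randomization and stratification). That section concedes that "we cannot determine cohort designation (breathing well or not) at randomization". The label comes later: "The neonatology provider will assess breathing, and at 30 seconds announce" the result (section 4, Initial Steps). By then the arm-specific script is with the team, and the intervention cannot be blinded (section 1, Rationale for Study Design).

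The primary endpoint is tested by cohort: "Analyses will be performed separately within each cohort" (Synopsis). Each cohort has its own "two-sided 5% level test", and in cohort 1 "172 EPT infants in each intervention arm achieves approximately 80% power" (section 7, Study Size Considerations).

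Two contingency rules follow.

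- **Imbalance.** "if a significant imbalance is noted in cohort 1 as assessed by the DSMC then a weighted minimization scheme will be used" to keep the arms balanced there. The stated trigger is a 30/70 split, or whatever the DSMC judges appropriate. The reason given is lost power: 78% at 40/60 and 73% at 30/70. The protocol puts the chance of a 30/70 or worse split below 0.001.
- **Cap.** At least 344 infants are required in cohort 1. If more than 65% of infants fall in cohort 2, "accrual to cohort 2 will be halted once 600 EPT infants are accrued". Yet the same section presents its power table as covering several cohort splits "since accrual to each cohort cannot be controlled".

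**The concern.** An infant's cohort does not exist when the infant is randomised, so no entry or allocation rule can act on it. Nobody can decline to randomise a future cohort 2 infant, which leaves the cap without a mechanism and without a stated consequence for infants beyond 600.

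The imbalance rule raises a further question. The steps up to 30 seconds are the same in both arms, so the share called not breathing well should differ between arms only by chance. The caller knows the arm, and the call has different consequences by arm: it bears on clamping time in Standard and on the choice of CPAP or PPV in VentFirst. A large by-arm difference would therefore question the label on which both primary comparisons rest. The protocol treats it as a loss of power and answers by changing the allocation.

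**Working it through.** **1. The plan's own figures.** Inputs from Study Size Considerations: failure rates 0.551 and 0.256, stratum shares 0.38 and 0.62, odds ratio 0.5, two-sided 5%, N = 344. The odds ratio gives VentFirst rates of 0.380 and 0.147. With n1 and n0 the arm sizes in a stratum of size n:

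- D = sum of (n1·n0/n)(p0 − p1)
- V0 = sum of (n1·n0/n)·p̄(1 − p̄)
- V1 = sum of (n1·n0/n)²·[p1(1 − p1)/n1 + p0(1 − p0)/n0]
- power = Φ((D − 1.96·√V0)/√V1)

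At 1:1, D = 11.40, √V0 = 4.087 and √V1 = 4.039, so power = Φ(0.84) = 79.9% (stated 80%). At 40/60 it is 77.9% or 78.7%, depending on which arm is larger (stated 78%); at 30/70 it is 71.8% or 73.9% (stated 73%). These figures reproduce and are not in dispute.

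**2. The cap.** If a share s breathes well, cohort 1 holds 600(1 − s)/s infants when cohort 2 reaches 600. Reaching 344 in cohort 1 then brings in 344·s/(1 − s) − 600 further cohort 2 infants.

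| s | Cohort 1 when cohort 2 = 600 | Further cohort 2 infants to reach 344 |
|---|---|---|
| 65% | 323 | 39 |
| 70% | 257 | 203 |
| 75% | 200 | 432 |

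The rule applies only above 65%, so cohort 1 is always below about 323 when it takes effect. The trial must then stop altogether, or go on randomising surplus cohort 2 infants.

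**3. How likely is 30/70 by chance?** Two-sided binomial with probability 0.5, by number of infants in cohort 1:

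| N | P(30/70 or worse) |
|---|---|
| 20 | 0.115 |
| 30 | 0.043 |
| 60 | 0.0027 |
| 100 | 8e-5 |
| 230 (about 2/3 of 344) | 1.2e-9 |
| 344 | 7e-14 |

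The stated bound of 0.001 holds at the full cohort size but not at 60 or fewer. No minimum N is set for the trigger.

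**4. What 30/70 means, and what re-weighting does.** With 37% in cohort 1 overall and 1:1 allocation, a 30/70 split means that 2 × 0.37 × 0.30 = 22% of one arm and 2 × 0.37 × 0.70 = 52% of the other are called not breathing well. Equal numbers of new cohort 1 infants would need an allocation of 0.518/(0.222 + 0.518) = 70% to the first arm. New cohort 2 infants then split 0.70 × 0.778 = 0.545 against 0.30 × 0.482 = 0.145, or about 79/21. The two label rates stay at 22% and 52%.

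**5. Possible bias (assumed rates).** The protocol gives no failure rates by breathing status. Assume 50% in cohort 1, 30% in cohort 2 and 40% in borderline infants, with no treatment effect. Move 10% of one arm from cohort 2 to cohort 1:

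- cohort 1: (0.37 × 0.50 + 0.10 × 0.40)/0.47 = 47.9%, a spurious benefit of 2.1 points;
- cohort 2: (0.63 × 0.30 − 0.10 × 0.40)/0.53 = 28.1%, a spurious benefit of 1.9 points.

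Both errors favour the same arm. Moving 15% gives 2.9 and 3.1 points.

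**The case against.** Much can be said for the plan. It admits openly that cohort is unknown at randomisation. The cohorts have observable definitions (apneic or gasping; crying or breathing regularly), the call is scripted and recorded, audio may be used to check it, and the ultrasounds for the primary endpoint are read blind to arm. Both rules cover contingencies that the plan does not expect: 50–65% breathing well is anticipated, and 600 + 344 = 944 is close to 940. These points limit the risk, but they supply no mechanism for the cap and no reason to answer a labelling difference by changing allocation.

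Four stronger readings are tempting, and the document does not support them.

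- **That minimisation cannot be run.** A biased coin driven by running cohort 1 totals is feasible. It cannot use the current infant's cohort, and it would tilt all allocation.
- **That 30/70 proves biased labelling.** At 20–30 infants chance alone gives it in 4–12% of cases. Stimulation that differs by arm before 30 seconds, or unequal losses after randomisation, could also produce it.
- **That nothing happens short of 30/70.** The DSMC may act at its discretion. Re-weighting is, however, the only remedy stated.
- **That infants beyond 600 would be discarded, breaking intention to treat.** No text says so. The Analysis Plan covers all randomised eligible infants. The gap is that their handling is not stated.

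An all-randomised comparison also averages over effects that the plan expects to differ by cohort, which is its reason for separate tests. That argues for a supporting role beside the cohort-specific tests.

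**Conclusion.** The point holds in two parts. First, the halt on cohort 2 cannot operate as written together with the 344 minimum: when it takes effect, cohort 1 is short by at least about 21 infants (344 − 323), and by 87 at a 70% share (344 − 257). Second, the stated response to a cohort 1 imbalance would leave any arm-dependent labelling in both primary comparisons and remove its most visible sign. At 100 or more cohort 1 infants chance is not a credible cause of 30/70; at 20–30 it is.

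The size of any bias is not known. About 2 points for 10% relabelling rests wholly on assumed failure rates and compares with design differences of 14 and 12.5 points. The chance probabilities treat infants as independent, including twins, who share an allocation. Nothing here shows that labelling will differ by arm. Because the plan expects neither rule to be needed, this is a should-fix.

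**What to change.** **Accrual.** Remove the halt on cohort 2 alone. State which of 940, 344 and 600 governs, and that every randomised infant is analysed. If 940 governs, give cohort 1 power for the shares that the cap was meant to address, using the formula above at odds ratio 0.5:

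| Breathing share | Cohort 1 at N = 940 | Power | Total N if 344 governs, 344/(1 − s) |
|---|---|---|---|
| 65% | 329 | 78% | 983 |
| 70% | 282 | 72% | 1147 |
| 75% | 235 | 64% | 1376 |

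**Imbalance.** Keep 1:1 stratified blocks throughout. Replace re-weighting with a DSMC comparison, by arm, of the proportion called not breathing well among all randomised infants, with a minimum N and a stated threshold. Two-sided p < 0.01 is one choice: at N = 940 the standard error is √(0.37 × 0.63 × 2/470) = 0.0315, so the threshold is 2.576 × 0.0315, or about 8 points. Crossing it would lead to an audit of delivery scripts and any audio, and to retraining in the breathing call.

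**Analysis.** Add, as a sensitivity analysis beside the cohort-specific primary tests, an all-randomised comparison of the primary endpoint that ignores cohort and is stratified by gestational age. It cannot be affected by the label.

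**Cost.** Protocol wording, a routine DSMC table and one analysis of data already collected. The real price lies in the accrual decision: power in cohort 1 below 80% if 940 governs, or a larger trial if 344 does.

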### **Primary endpoint**

The primary endpoint is based upon the central review evaluation and is the proportion of EPT infants who are alive without any grade IVH (including grade I germinal matrix hemorrhage) on head ultrasound obtained 7-10 days following birth. EPTs will be followed until 36 weeks post-menstrual age or discharge home, whichever comes first.

### **Primary hypothesis**

For each cohort, the primary null hypothesis of the study is that there is no difference between the proportions of EPT infants who are alive without any grade IVH on head ultrasound obtained 7-10 days from birth for Standard versus VentFirst. The alternative hypothesis of the study is that EPT are less likely to have IVH on head ultrasound obtained 7-10 days from birth if they receive assisted ventilation from 30 to 120 seconds followed by cord clamping, compared to those with cords clamped at 30-60 seconds, followed by assisted ventilation.

$$H_0: p_{\text{Standard}} = p_{\text{VentFirst}}$$

$$H_a: p_{\text{Standard}} \neq p_{\text{VentFirst}}$$

### **Study Size Considerations**

It is hypothesized that the investigational approach (VentFirst) improves outcomes in both cohorts with a greater effect in cohort 1 (not breathing

well), thus, the assumption of a common effect is violated and the two cohorts will be assessed separately. However, target sample size is based upon attaining a sufficient number of accruals to both cohorts. Based on discussions with investigators who have recently conducted delayed cord clamping trials in preterm infants, in addition to experience in our own Pilot Trial, it is anticipated that ~50-65% of EPTs infants will be categorized as ‘breathing well.’

The Cochrane meta-analysis of the effect of timing of umbilical cord clamping in preterm infants (delayed 30 or more seconds versus immediate) reported an estimated odds ratio (95% CI) of 0.59 (0.41-0.85) for survival without IVH. The Cochrane analysis included some infants up to 37 weeks gestational age where the differences in outcome affected by DCC may not be as large as might be expected in a cohort restricted to more immature infants. Furthermore, by restricting Cohort 1 to EPT infants who are not breathing well, it is hypothesized that the outcome effect will be even greater. Therefore, for this study we expect to see a larger reduction in our primary endpoint in the EPT infants in cohort 1 (odds ratio of 0.5) and a reduction on the order of magnitude observed in the Cochrane analysis or slightly more (odds ratio of 0.59 or 0.55) in the EPT infants in cohort 2.

Within each site, infants will be stratified by gestational age (GA 230/7 to 256/7 weeks; GA 260/7 to 286/7 weeks). Numbers of inborn infants 24-28 weeks’ GA without major birth defects at Vermont Oxford Network (VON) centers in the United States (670 centers) born in 2013 were used as the baseline estimates of the primary event rate. The information is summarized in the following table.

| Strata:
GA week/day                 | Proportion of newborns
in each strata | “Success”
% Alive without
IVH at day 7-10 | “Failure”
1-%Success |
|----------------------------------------|------------------------------------------|-------------------------------------------------|-------------------------|
| 23 0/7 to 25 6/7 | 0.38                                     | 44.9%                                           | 55.1%                   |
| 26 0/7 to 28 6/7 | 0.62                                     | 74.4%                                           | 25.6%                   |
| combined                               | 1.00                                     | 63.0%                                           | 37.0%                   |

We note that for sample size calculations we do not have numbers by site and thus assume a common effect, resulting in calculations that are based upon a randomized stratified design, which divides the sample among 2 strata at the assumed proportions observed in the VON data, assuming an uncorrected Cochran-Mantel-Haenszel test statistic with a two-sided 5% level test for *each* cohort, separately. Specifically, optimal target accrual for

the primary cohort of interest (cohort 1), summed across all strata, of 172 EPT infants in each intervention arm achieves approximately 80% power to test for a null odds ratio of 1.0 versus an alternative odds ratio of 0.5 (or a difference of 14% in rates). For cohort 2, optimal target accrual of 298 EPT infants in each intervention arm achieves approximately 80% power to test for a null odds ratio of 1.0 versus an alternative odds ratio of 0.55 (or a difference in rates of 12.5%). Shown in the table are estimated power calculations to assess each cohort assuming varying accrual proportions to the two cohorts and alternative odds ratios since accrual to each cohort cannot be controlled. The PASS 11 Power Analysis and Sample Size package was used to generate the sample size estimates.

| For total target accrual of N=940 EPT infants (N=N 1 +N 2 )
Assuming equal allocation (1:1) to intervention arms within each breathing cohort |                                                |                                               |                                        |          |          |
|------------------------------------------------------------------------------------------------------------------------------------------------------------------------|------------------------------------------------|-----------------------------------------------|----------------------------------------|----------|----------|
| Outcome                                                                                                                                                                | Sample size
N 1 , N 2 | Proportion
N 1 : N 2 | Alternative odds
ratio (difference) | Power    |          |
|                                                                                                                                                                        |                                                |                                               |                                        | Cohort 1 | Cohort 2 |
| Target*                                                                                                                                                                | 344, 596                                       | 37%:63%                                       | 0.50 (14%)                             | 80%      | 96%      |
|                                                                                                                                                                        |                                                |                                               | 0.55 (12½%)                            | 68%      | 89%      |
|                                                                                                                                                                        |                                                |                                               | 0.59 (11%)                             | 58%      | 81%      |
| Possible                                                                                                                                                               | 376, 564                                       | 40%:60%                                       | 0.50 (14%)                             | 83%      | 95%      |
|                                                                                                                                                                        |                                                |                                               | 0.55 (12½%)                            | 72%      | 88%      |
|                                                                                                                                                                        |                                                |                                               | 0.59 (11%)                             | 62%      | 79%      |
| Possible                                                                                                                                                               | 470, 470                                       | 50%:50%                                       | 0.50 (14%)                             | 91%      | 91%      |
|                                                                                                                                                                        |                                                |                                               | 0.55 (12½%)                            | 81%      | 81%      |
|                                                                                                                                                                        |                                                |                                               | 0.59 (11%)                             | 72%      | 72%      |
| * target accruals & hypothesized odd ratio alternatives per cohort are noted in bold                                                                                   |                                                |                                               |                                        |          |          |

If we set total target accrual to 940 eligible EPT infants and assume that at least 37% of accruals fall into cohort 1 then we will have approximately 80% power to detect an odds ratio of 0.5 for VentFirst compared to Standard for cohort 1 and we will have approximately 81% power to detect an odds ratio of 0.59 for VentFirst compared to Standard for cohort 2. Power increases for cohort 1 assessment as the proportion of accruals to that cohort increases and decreases in cohort 2 to as low as 72% for an odds ratio of 0.6. However, increasing our ability to assess the primary hypothesis at the cost of reducing the secondary is reasonable and still provides sufficient power to detect an odds ratio of 0.55. Given these conditions we will require accrual of at least 344 EPT infants to Cohort 1. If our assumptions on accrual proportions are incorrect and more than 65% of EPT infants are being accrued to cohort 2 then accrual to cohort 2 will be halted once 600 EPT infants are accrued.

